### 2.4. Outcomes

Two of the most accepted scales in pediatric rehabilitation will be used, quantifying gross motor function from different aspects.

The first is the Gross Motor Function Measure (GMFM). Gross motor function and mobility have important roles for classification, assessment, and research involving children with neuromotor disorders [42,43,44]. The Gross Motor Function Measure [45] could be currently considered as gold standard for the quantification of gross motor function in the pediatric rehabilitation. These follow ups of thousands of children with cerebral palsy described the long-term development of their gross motor function and defined five unalterable levels of severity. By the age of six, stability over time on the prognosticated level of mobility is expected [45]. Even though the GMFM was not designed to assess outcomes of therapeutic interventions, some authors have used its centiles to compare individual effects. The use of the reference percentiles for the GMFM as outcome make it possible to estimate the change between two subsequent assessments and to directly compare gross motor improvement across ages and Gross Motor Function Classification System (GMFCS) levels. On the other hand, uncompleted items of GMFM assessments are used as short-term therapeutic goals and, therefore, individually controlled comparison of the rate of acquisition of gross motor function seems to be possible within each range. 

The Infant Motor Profile (IMP) scale [46] is another evidence-based method of assessing infant motor behavior. It not only quantifies motor milestones, but also tests movement quality by analyzing five factors: variability, adaptation, symmetry, fluency, and capacity. The advantage of this scale is that the assessment is performed through video recording, allowing us to have a dedicated clinical evaluator blinded to the type of intervention. 

### 2.5. Other Variables

Age.Diagnosis.Locomotion stage.Gross Motor Function Classification System.Previous and concomitant physiotherapy treatments.Occupational therapy.Hydrotherapy.Surgery.Botulinum toxin.Geographic background.

As we have mentioned previously, the participants in this research, within their care routine and according to the health protocols established in the Service, will be assigned to one of the following two study groups:Intervention group: patients under Vojta therapy intervention.Control group: patients under regular physiotherapy intervention.

### 2.6. Sample Size Calculation and Statistical Analysis

Sample size calculation: The prevalence of cerebral palsy is 2.08 cases/1000 births. To obtain a good sample security, 30 subjects for each of the groups to be evaluated offer a confidence interval of 95% with a security of 10.

The initial GMFM and IMP score will be divided by the child’s months of age to calculate the rate of acquisition of their items so far. This calculation represents the mean distribution of the acquisition of these motor items. The acceleration values will be used to avoid errors in the assumption of how these items were acquired, since the tendency is to be exponential at these ages. The net values obtained in the valuation will not be considered, but the rate with which they have been obtained as a function of time will be. The rate of this development without intervention will be calculated at the time of the initial assessment, relative to the age of the patient. The proportion of the score necessary to obtain in the next two months to be able to accelerate that rate, instead of following the same previous trajectory, will be an unknown concept for all therapists and examiners.

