#### 2.3.1. Inclusion Criteria

Male and female children between 0 and 36 months, with a risk of neurological alteration or diagnosis of cerebral palsy or neuromotor disease, who are admitted for assessment and/or treatment according to the Vojta therapy methodology or conventional treatment in the Physical and Rehabilitation Medicine Service will be included in this study. The diagnosis may be clinical and/or supported by the presence of lesions in complementary tests. Due to the fact that the diagnosis of cerebral palsy is confirmed in many cases after one year of life, the data of children in treatment for risk of neurological alteration will only be included retrospectively when said diagnosis has been confirmed. Younger children have not received a definite diagnosis of CP yet, but, based on the presence of lesions determined by magnetic resonance imaging, their risk of developing CP was estimated to be sufficiently high to justify their inclusion in the CP group. 

Parents or guardians must sign the informed consent that will allow us to use their data on therapeutic results, always in a pseudonymized (coded) way, guaranteeing confidentiality. 

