### Statistical Methods

Statistical analysis will be performed using the SPSS 27.0 statistical software for Windows (SPSS Inc., Chicago, IL, USA; version 27.0). The normality of the sample will be checked using the Shapiro–Wilk test, and if it follows a normal distribution, an analysis of variance (ANOVA) of repeated measures p will be used, with time (pre-treatment and post-treatment) as an intra-group factor, and Vojta and conventional physiotherapy groups as the inter-group factor, all with a Bonferroni correction. Statistical analysis will be performed with a confidence level of 95%, so a *p*-value of <0.05 will be considered significant.

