## 4. Discussion and Ethical–Legal Aspects

Completed assessment data of four subjects has been collected to date, as two subjects withdrew prematurely or did not sign the consent form. Recruitment is currently ongoing at our first site and no results report is available due to the small sample. 

The baseline scoring of GMFM at initial assessment is related to the age of the child in order to understand the rate of items acquisition so far. The aim of this study is not to compare absolute values of GMFM between different subjects according to their age and, therefore, if the children are born preterm, the chronological age is considered. This allows us to plot changes due to spontaneous and therapeutic gross motor experience after birth. 

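### The sample size is justified by the birth prevalence of cerebral palsy and a precision figure with no unit; neither bears on the planned group comparison, and the figure cannot be reproduced

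*Protocol article*

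**What the plan says.** The sample-size paragraph in section 2.6 has two sentences. The first is "The prevalence of cerebral palsy is 2.08 cases/1000 births". The second says that "30 subjects for each of the groups to be evaluated offer a confidence interval of 95% with a security of 10". No unit, parameter or formula is attached to the 10.

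The comparison that the trial makes is described elsewhere. Under Statistical Methods it is a repeated-measures ANOVA "with time (pre-treatment and post-treatment) as an intra-group factor, and Vojta and conventional physiotherapy groups as the inter-group factor", and "Statistical analysis will be performed with a confidence level of 95%, so a *p*-value of <0.05 will be considered significant". Section 2.6 also fixes the scale of analysis: "The net values obtained in the valuation will not be considered, but the rate with which they have been obtained as a function of time". Section 2.3.1 enrols children "with a risk of neurological alteration or diagnosis of cerebral palsy or neuromotor disease, who are admitted for assessment and/or treatment", and section 2.3.2 removes children in whom cerebral palsy is not later confirmed.

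**The concern.** The only stated support for 30 per group is a population prevalence and a precision claim. Prevalence would matter if the trial estimated how common cerebral palsy is, but it estimates no prevalence. It compares two treatments in children already referred, on a continuous outcome, and birth prevalence enters neither the effect nor the variance of that comparison.

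The precision claim is a positive quantitative statement, so it can be checked. If it cannot be tied to the planned test, the article does not tell the reader which differences the trial can detect. A non-significant result could then be taken as evidence that the two treatments perform alike when the interval is in fact wide.

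**Working it through.** **Inputs from the article:** prevalence 2.08/1000, so p = 0.00208; 30 per group; 95% confidence; 5% significance (section 2.6 and Statistical Methods). **Assumed:** two-sided testing, because the article does not state sidedness.

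**Step 1. Try to reproduce the stated figure as precision for a proportion.** The formula is n = z² p(1−p)/d², with z = 1.96.

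| p | d | n needed |
|---|---|---|
| 0.00208 | 10 points | 0.8 |
| 0.00208 | 5 points | 3.2 |
| 0.00208 | 1 point | 79.7 |
| 0.00208 | 10% of p | about 184,300 |
| 0.5 | 10 points | 96.0 |
| 0.5 | 5 points | 384 |

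One-sided versions at 10 points give 0.6 (p = 0.00208) and 67.6 (p = 0.5). No variant gives 30, or 60 in total.

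In the other direction, with n = 30:
- p = 0.5: 1.96 × √(0.25/30) = 0.179, or ±17.9 points.
- p = 0.00208: 1.96 × √(0.00208 × 0.99792/30) = 0.0163, or ±1.6 points. This is nominal only: np = 30 × 0.00208 = 0.06, where the normal approximation is not valid.
- ±10 points requires p(1−p) = 30 × 0.01/3.84 = 0.078, so p ≈ 0.085. The article gives no such value.

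**Step 2. Try other meanings of the 10.** For means, the 95% half-width with 30 per group is:
- one group mean: t(0.975; 29)/√30 = 0.373 SD
- difference between groups: t(0.975; 58) × √(2/30) = 2.002 × 0.258 = 0.517 SD

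If the 10 meant score points, it would be met for the group difference when SD ≤ 10/0.517 = 19.3, and for one group mean when SD ≤ 10/0.373 = 26.8. If it meant 10% of the mean, the same limits apply to the coefficient of variation (about 19% and 27%). The article states no SD or coefficient of variation, so these readings can be neither confirmed nor refuted.

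**Step 3. What 30 per group gives for the planned test.** With two time points, the time-by-group interaction equals a two-sample t test on change. In units of the SD of the pre-post change in the analysed rate, with no baseline adjustment:
- 95% half-width for the between-group difference in change: 0.52 SD
- difference detectable with 80% power (noncentral t): 0.74 SD
- power for 0.5 SD: 48%; 80% power for that difference would need 64 per group

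**Step 4. The unit matters.** In SDs of a single measurement with equal variances, the detectable difference is 0.736 × √(2(1−r)), where r is the pre-post correlation. This gives 0.93 at r = 0.2, 0.74 at r = 0.5 and 0.47 at r = 0.8. The article does not give r, so these values are an assumed range.

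**Step 5. An assumed scenario with 20 evaluable per group:** half-width 0.64 SD, 80% power for 0.91 SD, and 34% power for 0.5 SD.

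**The case against.** The strongest reply is that a number without a unit cannot be shown to be false. Percentage points are only one reading, and no analysed outcome is a proportion. Ten score points, or 10% of the mean, could be met if the spread were small enough. This stands as far as it goes. A reader might infer that 30 per group fails to give the claimed precision for every comparison in the trial, but the article does not support that, because it gives no SD. The reply does not rescue the claim either. Section 2.6 says net scores will not be considered, which leaves the score-points reading attached to an outcome the plan sets aside, and nothing in the article supports the percentage reading.

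A reader might also infer that 30 was calculated from the prevalence. The article sets the two side by side and shows no derivation, so the prevalence is offered as context for a number that does not follow from it.

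A third tempting step is to read a one-third loss rate from section 4: "Completed assessment data of four subjects has been collected to date, as two subjects withdrew prematurely or did not sign the consent form". That sentence mixes withdrawals with families who did not consent, and the latter were never participants. The split is not given, and at most two children are involved. The wording in section 2.6 may also mean 30 evaluable children per group. A smaller evaluable number is worth showing because section 2.3.2 removes data after enrolment, but only as an assumption.

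Finally, a condensed article may leave the effect size, SD and power to a fuller document. Their absence is not the point here. The point is the claim that the article does make.

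**Conclusion.** The point holds in this form: the prevalence is irrelevant to the planned comparison, and the precision claim is undefined, cannot be reproduced at n = 30 from the stated prevalence or from p = 0.5, and does not describe the time-by-group test. A true difference of half an SD of change would be missed about half the time (power 48%).

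The half-width and power figures assume 30 evaluable children per group, a two-sided 5% level, no baseline adjustment, and SD defined as that of the pre-post change in the analysed rate. The difference of 0.5 SD is illustrative, since the article names no target difference. The finding does not show that 30 per group is the wrong number, only that the reason given does not support it.

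**What to change.** In section 2.6, delete the prevalence sentence and the claim that 30 per group "offer a confidence interval of 95% with a security of 10". The authors should state the actual basis for 30 per group. The article does not give one, and a reviewer should not supply it. Then add text such as:

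> With 30 evaluable children per group and a two-sided 5% level, the 95% confidence interval for the between-group difference in change has a half-width of about 0.52 SD. Power is 80% for a difference of about 0.74 SD and 48% for 0.5 SD. SD is the standard deviation of the pre-post change in the analysed rate. A non-significant result will not be read as no difference.

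If figures for fewer children are shown (20 per group: half-width 0.64 SD, 80% power for 0.91 SD), label them as an assumed scenario for the post-enrolment exclusions in section 2.3.2, not as a loss rate observed in section 4.

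The cost is wording only. The sample size, design and analysis are unchanged and no extra patients are needed, but the stated ability to detect a difference will look less favourable.

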### 2.7. Intervention

Vojta therapy: The therapist applied pressure to defined zones on the body whilst positioned in prone, supine, and side-lying aspects, where the stimulus leads to automatically and involuntarily complex movement. The parents were also instructed on at least one of the exercises from the first session, after the initial assessment. The home program was progressively increased and supervised until the three therapy positions were mastered, during weekly or fortnightly follow ups. The recommended dose was four times per day at home, in session no longer than 15–20 min; however, the daily frequency of each family due to different availability was also taken into account. The frequency of the dose was divided into four groups: families who could carry on therapy (a) three times per day, (b) four times per day, (c) one or two times per day, (d) less than seven times per week or therapy at the clinic. 

Conventional physiotherapy: Conventional physiotherapy intervention included goal-directed functional training based on tasks. These motor skills will be performed in enhanced and adapted settings, but as similar as possible to the usual activities of daily living. Families and children participated in the goal setting, and the approach will focus on overcoming the limitations of the activities to reach these goals, instead of the modification of the movement patterns. This intervention is founded in motor learning and behavioral neuroscience, focusing on participation and activity acquisition. 

## 3. Methods and Timeline

Phase 1. Initial Assessment: Children who go to the rehabilitation center where they have been referred will be treated, an initial routine clinical examination will be performed, including: Personal/medical data collection.GMFM quantification.Treatment with the physiotherapist.Training of the parents in the home program.Recording for the IMP quantification.

Phase 2. Intervention period (2 months): The assignment to the therapist will be randomized according to the needs of the service, where each therapist will adapt the treatment according to the initial assessment. Both assessors and therapist cannot be blinded to the allocation or treatment, and both required live-direct performance. An external assessor (blind to both) will be able to score the IMP recordings. 

Children will receive weekly or fortnightly treatment, and their parents, family members, or carer will be trained in carrying out a home program. Each therapist will adapt the treatment according to the initial evaluation, as is usually performed in the rehabilitation service. During the treatment sessions, the physiotherapist will apply the therapy directly, either based on Vojta therapy or conventional physiotherapy. The frequency of repetition of the treatment at home and in the hospital will be recorded, depending on the availability of each family and the normal functioning of the service.

Phase 3. Second assessment at 2 months (±1 week, depending on follow up appointments).

Collection of data on the possible changes made in previous treatments and the frequency of home treatment (possible incidents due to illness or family limitations).GMFM quantification.Recording necessary for IMP quantification.

Children carried on clinically with the intervention, but this short period would allow us to attribute changes to RL, controlling better the influence of other factor (such as age maturation or other therapy inputs).

Study length. The data collection will be carried out for 4 years from the approval of the CEI. Only patients receiving healthcare with any of the therapies under investigation after authorization by the CEI will be included.

### Statistical Methods

Statistical analysis will be performed using the SPSS 27.0 statistical software for Windows (SPSS Inc., Chicago, IL, USA; version 27.0). The normality of the sample will be checked using the Shapiro–Wilk test, and if it follows a normal distribution, an analysis of variance (ANOVA) of repeated measures p will be used, with time (pre-treatment and post-treatment) as an intra-group factor, and Vojta and conventional physiotherapy groups as the inter-group factor, all with a Bonferroni correction. Statistical analysis will be performed with a confidence level of 95%, so a *p*-value of <0.05 will be considered significant.

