## 2. Materials and Methods

### 2.1. Study Design

A pseudo-randomized clinical trial has been designed that will assess gross motor function before the physiotherapy intervention (with Vojta therapy or conventional physiotherapy intervention, such as environmental enrichment and task-specific training) and two months after its application. The clinical trial has been conducted according to the consolidated standards of reporting trials (CONSORT) statement [40]. The current treatment protocol is described according to the recommendations of SPIRIT [41].

Patients are assigned to one treatment or another following criteria of immediacy as part of the regular routine of the rehabilitation service. Therefore, the randomization of the sample is possible following the natural ordering of the rehabilitation service where the study is carried out. The participants in this research, within their care routine and according to the health protocols established in the service, will be assigned to one of the two study groups:Intervention group: patients under Vojta Therapy intervention [17,18,19,20,21,22,23,24,25,26,27,28]Control group: patients under regular physiotherapy intervention, such as environmental enrichment and task-specific training [25]

This methodology will be useful to provide a service evaluation of the operation of the rehabilitation service itself.

Neither the therapists nor the evaluators of the GMFM may be blinded to the type of treatment administered due to the organization of the rehabilitation service where the study is carried out, as well as the “face-to-face” requirements for carrying out the Vojta therapy and the evaluation of that scale. However, the assessment of the Infant Motor Profile (IMP) is performed by observing a protocolized video recording. This allows the quantification of this factor by an evaluator external to the service (in this case the external principal investigator). This will not only allow us to blind the evaluator regarding the type of intervention that the child receives, but also whether the video belongs to pre- or post-intervention groups. To do this, the videos will be sent after being encrypted and randomized for quantification. 

The study was approved by the Research Ethics Committee of the University of Murcia (1823/2018) and Comité de Ética de la Investigación de A Coruña-Ferrol (2022/099). This trial has been registered under the following code: ClinicalTrials.gov Identifier: NCT0609261.

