### 2.3. Participants

Participant selection allows the randomization of the sample following the natural ordering of the rehabilitation service where the study is carried out. The assignment of children to their different therapists is performed according to the available treatment times of the latter. In other words, patients are assigned to one treatment or another following criteria of immediacy as part of the regular routine of the rehabilitation service. Therefore, the randomization will be carried out through the needs of the service, as is already the case.

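### The only stated between-arm analysis, a two-time-point repeated-measures ANOVA, fixes the baseline coefficient at 1; a baseline-adjusted comparison would usually be more precise, with the change-score result kept beside it because allocation is by service slot

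*Protocol article*

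**What the plan says.** The Statistical Methods section gives one analysis that compares the arms. If normality is supported, "an analysis of variance (ANOVA) of repeated measures p will be used, with time (pre-treatment and post-treatment) as an intra-group factor". Treatment arm is the factor that varies between children, and a Bonferroni correction applies throughout. The section names no covariate and does not say whether the group, time or group-by-time term is the treatment test.

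The baseline is available: the trial "will assess gross motor function before the physiotherapy intervention" and again at two months (section 2.1), and section 3 lists GMFM and the IMP recording at both visits.

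The analysed quantity is a rate: "The net values obtained in the valuation will not be considered, but the rate with which they have been obtained as a function of time" (section 2.6). For GMFM, section 4 defines the pre-intervention rate as total score over age. A second calculation assigns all items to the last two months before treatment. The intervention-period rate counts only points newly gained in the two months.

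On allocation, section 2.3 says that "patients are assigned to one treatment or another following criteria of immediacy", and section 2.1 calls the design pseudo-randomized.

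**The concern.** A change score subtracts each child's baseline in full. That is the best use of the baseline only if the slope of the 2-month value on the baseline value is 1. With equal SDs the slope equals the correlation, which is below 1 when scores carry measurement error. The subtraction then adds baseline noise to the arm comparison, and a chance difference at baseline passes into the estimate.

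For GMFM the case is plainer. The pre and post values are different quantities measured over different windows, so nothing ties the slope to 1. Section 4 spells out that definition for GMFM only. For IMP the argument is the general one.

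At stake is the precision of the only comparison that can separate Vojta therapy from conventional care. The article states no power or effect size that would show a margin to spare.

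**Working it through.** **Inputs from the article.** 30 children per arm (section 2.6); two time points, two arms, no covariate, 95% confidence (Statistical Methods). Two-sided testing is assumed.

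**Inputs not in the article.** The pre-post correlation r and the ratio k = post SD / pre SD. Both are assumed and shown as ranges.

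**The plan's own figure.** Section 2.6 says "30 subjects for each of the groups to be evaluated offer a confidence interval of 95% with a security of 10", next to a prevalence of 2.08 per 1000. Reading the 10 as ±10 percentage points, n = 1.96² × p(1−p) / 0.10² gives 0.80 (1 subject) at p = 0.00208 and 96.04 (97 subjects) at p = 0.5. Thirty does not follow from these inputs. That is a separate matter; 30 per arm is taken as given here.

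**Step 1: equivalence.** In one simulated data set with 30 per arm, the group-by-time F was 7.3665 and the squared t on post minus pre was 7.3665. The identity concerns this term only. The group main effect averages pre with post and is a different, diluted test.

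**Step 2: precision with equal SDs (k = 1).** Per-arm variance is 2(1−r)SD² for change and (1−r²)SD² for ANCOVA, so the ratio is (1+r)/2. Half-widths in SD units are:
- change: t(58 df) × √[2(1−r) × 2/30]
- ANCOVA: t(57 df) × √[(1−r²) × 2/30 × (1 + 1/56)]

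| r | Variance ratio | Half-width, change | Half-width, ANCOVA | CI narrower by |
|---|---|---|---|---|
| 0.3 | 0.65 | 0.612 | 0.498 | 19% |
| 0.5 | 0.75 | 0.517 | 0.452 | 13% |
| 0.7 | 0.85 | 0.400 | 0.373 | 7% |
| 0.9 | 0.95 | 0.231 | 0.227 | 1.6% |
| 0.95 | 0.975 | 0.163 | 0.163 | 0.3% |

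At r = 0.98 the ANCOVA interval is 0.4% wider, because the small-sample penalty outweighs the gain. To match ANCOVA with 30 per arm, the change score needs 30 × 2/(1+r): 40 per arm at r = 0.5, 36 at 0.7, 32 at 0.9. For an assumed difference of 0.5 SD, power (normal approximation) rises from 49% to 61% at r = 0.5 and from 71% to 77% at r = 0.7.

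**Step 3: precision with unequal SDs.** The variance ratio is k²(1−r²) / (1 + k² − 2rk) and the slope is r × k.

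| k | r = 0.3 | r = 0.5 | r = 0.7 | r = 0.9 |
|---|---|---|---|---|
| 0.5 | 0.239 | 0.250 | 0.232 | 0.136 |
| 2 | 0.958 | 1.000 | 0.927 | 0.543 |

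At k = 2, r = 0.5 the slope is 2 × 0.5 = 1: no gain and no baseline-driven shift. At k = 2, r = 0.7 the slope is 1.4, and a chance gap would favour the arm that starts higher. Before the small-sample penalty the ratio never exceeds 1.

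**Step 4: a baseline gap of 0.5 SD with no treatment effect** (equal SDs, 4000 simulated trials per setting). The SE of a chance gap is √(2/30) = 0.258 SD, so 0.5 SD is 0.5/0.258 = 1.9 SE.

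| Type of gap | r | Change score: shift, rejection | ANCOVA: shift, rejection |
|---|---|---|---|
| Chance | 0.5 | −0.26, 13% | about 0, 5% |
| Chance | 0.7 | −0.15, 9% | about 0, 5% |
| Stable, systematic | 0.5 | about 0, 5% | +0.25, 18% |
| Stable, systematic | 0.7 | about 0, 5% | +0.15, 11% |

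The shifts agree with (1−r) × 0.5 = 0.25 and 0.15, up to simulation error.

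**The case against.** The strongest objection concerns bias. A reader might infer that a baseline covariate stops any baseline gap from moving the result. The article does not support that. Children go to whichever therapist has a free slot, so a gap may be systematic, and Step 4 shows ANCOVA then producing the error it was meant to prevent. This stands, and it is why the change-score result has to stay.

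Second, the equal-SD figures may not describe the planned rate variable, and r may be high over two months. This also stands. It makes the size of the gain uncertain, but does not make the change score the more precise choice beyond a trivial penalty at very high r.

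Third, the change-score test is not invalid. Averaged over chance gaps under random allocation it keeps its 5% error rate, and a 0.5 SD gap is an uncommon draw. This stands: for chance gaps the point is about precision and about the result in the trial at hand.

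Fourth, a change contrast matches the question, since section 2.3.2 says that children are compared only to themselves. But the between-arm effect is still a difference between groups, and ANCOVA estimates it while using each child's own baseline.

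Fifth, covariate models are often left to an analysis plan. Here the model is stated, so this is a choice open to comment. How age, GMFCS level and concomitant therapy will be modelled is not criticised.

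**Conclusion.** The point holds as a recommended improvement to the analysis. The stated model is, in its group-by-time term, a change-score comparison with the baseline coefficient fixed at 1, and the rate definitions for GMFM give no reason to expect that slope. With 30 per arm and equal SDs, adjustment narrows the 95% CI by 19%, 13% and 7% at r = 0.3, 0.5 and 0.7, by 1.6% at 0.9, and not usefully from 0.95 up. With k between 0.5 and 2 and r up to 0.9, the variance ratio runs from 0.14 to 1.00. The article gives neither r nor k, so no single figure can be claimed.

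Two stronger readings do not follow. The planned ANOVA is not shown to be invalid. Nor does ANCOVA make up for slot-based allocation: it corrects chance gaps under a linear baseline relation, and neither method is sure to be unbiased here. With ages from 0 to 36 months, adjusting for baseline rate alone is also not an adjustment for age.

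**What to change.** In Statistical Methods, make the between-arm analysis an ANCOVA: 2-month value as outcome, arm as factor, baseline value of the same measure as covariate, reporting the adjusted arm difference with its 95% CI. For GMFM, say which of the two pre-intervention rates in section 4 is the covariate. Keep the repeated-measures result as a sensitivity analysis and name group-by-time as its tested term. State in advance that a disagreement between the two will be reported as a limit on the conclusion, because allocation follows service slots.

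The cost is a few sentences and one degree of freedom, with no new data. The drawback is that two results may differ and have to be explained.
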